## 5. TREATMENT OF SUBJECTS

### 5.1 Investigational product/ treatment

#### 1. Inclusion

Information on the inclusion procedure is given in section 11.2 Recruitment and consent.

#### 2. Preoperative period

##### A. Without intervention (standard preoperative care)

Patients will undergo standard preoperative care according to Dutch guidelines(39). To collect data, two additional appointments will be combined with regular, preoperative outpatient clinic visits. Patients will undergo measurements regarding physical fitness, nutritional status and health status as shown in Appendix I.

##### B. With intervention (multimodal intensive prehabilitation program)

Additionally to the standard preoperative care, patients will undergo a multimodal intensive prehabilitation program prior to the scheduled elective procedure, including an exercise program, nutritional intervention, smoking cessation and psychological support. Patients will undergo prehabilitation throughout the full preoperative period. The surgical procedure will not be delayed due to this program. Since the preoperative period differs between the clusters regarding time and treatment, the time period for prehabilitation is not the same within all clusters. Therefore, patients will be divided into two groups based on their diagnosis and preoperative treatment as shown in the table below.

Table 3. Groups based on diagnosis and preoperative treatment

| Group: PREHAB LONG
Duration prehabilitation: >5 weeks | Group: PREHAB SHORT
Duration prehabilitation: <5 weeks |
|---------------------------------------------------------------------------|----------------------------------------------------------------------------|
| Pancreato-biliary cancer (after completing neo-adjuvant therapy)          | Hepatic colorectal cancer metastases                                       |
| Rectal cancer (after completing neo-adjuvant therapy)                     | Peritoneal carcinomatosis from colorectal cancer                           |
| Esophageal cancer (after completing neo-adjuvant therapy)                 | Colon cancer                                                               |
| Supratentorial meningioma                                                 | Abdominal aortic aneurysm (open and endovascular)                          |
| Hip arthrosis                                                             | Renal cancer                                                               |
| Osteosarcoma                                                              | Bladder cancer                                                             |
| Pulmonary cancer (after completing neo-adjuvant therapy)                  | Pancreato-biliary cancer without neo-adjuvant therapy                      |
|                                                                           | Pulmonary cancer without neo-adjuvant therapy                              |
|                                                                           | Thoracic aortic aneurysm                                                   |

|  |                       |
|--|-----------------------|
|  | Head and neck cancer  |
|  | Breast reconstruction |
|  | Mouth cancer          |
|  | Ovarian cancer        |
|  | Endometriosis         |

Despite differences in prehabilitation duration, general goals apply for each participating patients. The different disciplines (exercise program, nutritional intervention, psychological support, smoking cessation) involved in the prehabilitation program are described below.

### **2.B.1 Triage**

Triage will be performed focusing on anemia and disturbed glucose regulation. In case of abnormal blood levels patients will be referred to an internist. Patients will also be screened on frailty using the Geriatric 8 questionnaire. A geriatrist will be consulted in case a patient is screened at risk. The prehabilitation program will start after approval of the consulted physician.

### **2.B.2 Exercise program**

- Screening: all patients undergoing the multimodal intensive prehabilitation program will be screened for physical fitness according to the American College of Sports Medicine (ACSM) exercise preparticipation health screening questionnaire for exercise professionals. Patients screened at risk will be referred to a cardiologist or pulmonologist to undergo additional tests (e.g. ECG, spirometry, cardiopulmonary exercise test) to assess whether undergoing high intensity training (HIIT) during prehabilitation is safe.
- Assessment: the content of the exercise program will be adjusted based on a patient's estimated VO2 peak (submaximal Astrand-Rhyming test) and muscle strength (indirect 1RM).
- Goal: to increase physical fitness (estimated VO2 peak and indirect 1RM) by 10%.
- The content of the exercise program: to reach the goal, the exercise program consists of the following components:
  - *Endurance training*:
    - High intensity interval training (HIIT)
      - This supervised training (by 1st line physiotherapist) will be done
        - Group 'PREHAB LONG': two times a week
        - Group 'PREHAB SHORT': three times a week
      - The interval training duration is 28 minutes and performed with 4 intervals of moderate intensity (3 minutes) and 4 intervals of high intensity (4 minutes)
      - The workload is dosed at a percentage of estimated VO2 peak. High intensity is considered 90% of estimated VO2 peak
      - This interval training aims to reach levels of Borg 15-17 and >85%

of the age-predicted maximum heart rate, as long as the patient could effort the exercise

- Exercise may be performed on a bicycle, a rower, a treadmill and/or on other aerobic exercise machines

- *Resistance training*

- This supervised training (by 1st line physiotherapist) will be done
  - Group 'PREHAB LONG': two times a week
  - Group 'PREHAB SHORT': three times a week
- Strength training will be the same concept for all patients irrespective of VO2 peak
- The strength exercises are performed according to: 2 seconds of concentric strength and 2 seconds of eccentric strength.
- The strength training consists of two series of 10 repetitions of six exercises: leg press, chest press, abdominal crunch, lat pull down, low row and step up
  - In week 1 using 65% of calculated indirect 1RM (measured during assessment)
  - In week 2 using 70% of calculated indirect 1RM (measured during assessment)
  - In week 3 using 75% of calculated indirect 1RM (measured during assessment)
  - In week 4 using 80% of calculated indirect 1RM (measured during assessment)
- The last bout with 10 repetitions needs to be attainable. If this is not the case in the next session dosing will be 5-10% lower. If in the last bout it appears that exercises are too low (≥15 repetitions will be achieved), in the next sessions dosing will be 5-10% higher

- *Homework/counseling*

- The homework will be done at the days without supervised training
- Patients are instructed to aim at 60 minutes walking and/or cycling a day. If possible, patients can do more than 60 minutes of walking or cycling every day
- In case of lower exercise capacity it is advised to walk/cycle 2-3 times a day for periods of 20 minutes
- Also an electric bicycle, a stationary bicycle and/or a walking aid

(walker) may be necessary

- Instructions on breathing techniques will be given to reduce the risk of developing pneumonia postoperatively

- *Rest*

- Patients are instructed to take care of recovery and adequate rest and sleep
- From 3 days before surgery no high intensity interval training and strength training are done. The patient will continue with the homework/counseling (walking/cycling every day) and the dietary supplements

### **2.B.3 Nutritional intervention**

- Screening: a registered dietician will screen for a patient's nutritional status by Patient-Generated Subjective Global Assessment (PG-SGA).

- Assessment: a patient's body weight, length, 3-day food diary, hand grip strength and fat-free mass measured by Bioelectrical Impedance Analysis (BIA) are used to adjust the content of the nutritional intervention.

- Goal: to enhance the anabolic effect of physical training, to improve the lean body mass and to obtain or maintain an optimal nutritional status preoperatively

- The content of nutritional intervention includes:

- *Dietary advice*

- Aiming for optimal energy intake bases on screening and assessment
- Aiming for a protein intake of 1.5 – 1.8 g/kg daily

- *Protein supplementation*

- 30 g protein supplementation immediately following supervised training (within 1 hour) and before going to sleep

- *Vitamin supplementation*

- Vitamin D:

- Female patients, age <50 years with colored skin and/or little sun exposure
  - 10 µg vitamin D daily
- Female patients, age 50-69 years
  - 10 µg vitamin D daily
- Male patients, age <70 years
  - 10 µg vitamin D daily
- Female/male patients, age >70 years
  - 20 µg vitamin D daily

- Multivitamin: 50% of the recommended daily allowance supplementation

#### **2.B.4 Psychological support**

- Screening/assessment: psychological factors that may affect postoperative outcomes adversely will be identified by the Hospital Anxiety and Depression Scale (HADS).

- The content of psychological support: patients screened at risk will be seen by a trained psychologist to address a patient's anxieties, coping strategies and post-operative expectations. The goal of psychological support is to optimize psychological well-being and to provide ways of coping with surgery. If indicated, more session will follow preoperatively.

#### **2.B.4 Smoking cessation**

A smoke cessation program including intensive counseling and nicotine replacement therapy (NRT) will be offered to all patients during the weeks prior to the surgery. Approximately 15-20% of the patients in the study group are current smokers at the moment of cancer diagnosis. The goal is to achieve a smoke cessation percentage of 80.

#### **3. Surgery**

Surgery will be performed in the various departments of the Radboudumc by specialized attending surgeons. Surgical approach, including laparoscopic, endoscopic or open surgery will be at the discretion of the surgeon. Perioperative care will be followed by the Enhanced Recovery After Surgery (ERAS) program, which is an evidence-based multidisciplinary care plan(40). The ERAS program has been standardized care since more than 10 years now, and includes patient education, preoperative feeding, selected bowel preparation, multimodal analgesia, maintenance of perioperative normothermia, early oral intake and early mobilization, early removal of catheters and drains, and a pre-planned hospital stays according to clinical pathways.

#### **4. Post-operative period**

After discharging, patients will receive standard postoperative care according to Dutch guidelines(41). Questionnaires will be additionally performed at 6 and 12 months after surgery.

A 'subway line' map for each cluster will be designed to give a clear overview of treatment including the prehabilitation program for patients and health care workers.

### **5.2 Use of co-intervention**

Not applicable

### **5.3 Escape medication**

Not applicable

## **6. INVESTIGATIONAL PRODUCT**

Not applicable

## **7. NON-INVESTIGATIONAL PRODUCT**

Not applicable

## 8. METHODS

### 8.1 Study parameters/endpoints

#### 8.1.1 Main study parameter/endpoints

Primary outcomes that are studied in this trial include:

| Outcome                     | Tool used                        | Expressed in | Measured at      |
|-----------------------------|----------------------------------|--------------|------------------|
| Postoperative complications | Clavien-Dindo classification     | Score I-V    | Surgery +4 weeks |
|                             | Comprehensive Complication Index | Score        | Surgery +4 weeks |

Table 4. Primary study parameters

#### 8.1.2 Secondary study parameters/endpoints

The following secondary outcomes are studied in this cohort study:

| Outcome                                 | Tool used                                                                                     | Expressed in                | Measured at                                         |
|-----------------------------------------|-----------------------------------------------------------------------------------------------|-----------------------------|-----------------------------------------------------|
| Length of hospital stay (LOS)           | -                                                                                             | In days                     | Surgery +4 weeks                                    |
| Change in physical fitness and activity | Estimated VO 2 peak (submaximal Astrand-Rhyming test)                              | Milliliters/kilogram/minute | Baseline
Surgery -1 week                         |
|                                         | Indirect 1 repetition measures (1RM)                                                          | Weight in kilograms         | Baseline
Surgery -1 week                         |
|                                         | Physical activity (Short Questionnaire to Assess Health-enhancing physical activity (SQUASH)) | Minutes per week            | Baseline
Surgery +6 months
Surgery +12 months |
| Change in nutritional status            | Body weight                                                                                   | In kilograms                | Baseline
Surgery -1 week                         |
|                                         | Fat-free mass (Bio Impedance Analysis (BIA))                                                  | Weight in kilograms         | Baseline
Surgery -1 week                         |
|                                         | PG-SGA                                                                                        | Score (A, B or C)           | Baseline
Surgery -1 week                         |

|                                                                               |                                                                                                     |                                      |                                                                        |
|-------------------------------------------------------------------------------|-----------------------------------------------------------------------------------------------------|--------------------------------------|------------------------------------------------------------------------|
| Change in mental health                                                       | Health-related Quality of Life (SF-36)                                                              | Score                                | Baseline
Surgery -1 week
Surgery +6 months
Surgery +12 months |
|                                                                               | Health-related Quality of Life (EQ-5D-5L)                                                           | Score                                | Surgery +6 months                                                      |
| Change in innate immune response
(only in abdominal aortic aneurysm group) | Degree of immunoparalysis                                                                           | Monocyte HLA-DR (mHLA-DR) expression | Baseline
Prior to anesthesia
Surgery +2 days
Surgery +6 weeks |
| Preoperative health behavior                                                  | Questionnaire for patients in control group

Questionnaire for patients in intervention group |                                      | Surgery -1 week                                                        |
| Intervention adherence                                                        |                                                                                                     |                                      | Surgery -1 week                                                        |
| Costs due to complications                                                    |                                                                                                     |                                      | Surgery +4 weeks                                                       |
| Costs due to length of hospital stay                                          |                                                                                                     |                                      | Surgery +4 weeks                                                       |
| Budget impact analysis                                                        |                                                                                                     |                                      | Surgery +1 year                                                        |
| Cost-effectiveness                                                            |                                                                                                     |                                      | Surgery +1 year                                                        |
| Changes in patients volumes                                                   |                                                                                                     |                                      | Surgery +1 year                                                        |
| Shifts between 2nd and 1st line healthcare                                    |                                                                                                     |                                      | Surgery +1 year                                                        |

Table 5. Secondary study parameters

A more detailed description of the outcome parameters is given in section 8.3 Study procedures.

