## 2. OBJECTIVES

Primary Objective: To determine the effects of a multimodal intensive prehabilitation program a high-risk patient group on complications (Clavien Dindo score and Comprehensive Complication Index (CCI) score)

Secondary Objective(s): To investigate the effects of multimodal intensive personalized prehabilitation on an:

- Individual patient's level, i.e. length of hospital stay (in days), physical fitness (estimated  $VO_2$  peak, indirect 1 repetition measures, physical activity), nutritional status (body weight, fat-free mass, Patient-Generated Subjective Global Assessment (PG-SGA), mental health (HRQoL), intervention adherence
- Mechanistic level, i.e. innate immune response (degree of immunoparalysis)
- Hospital-efficiency level: costs due to complications, costs due to length of hospital stay, budget impact, cost-effectiveness
- Macro-economic level: changes in patients volumes, shifts in care between 2nd and 1st line healthcare

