### 3. STUDY DESIGN

This is a monocenter stepped-wedge cluster randomized trial of patients aged >16 years undergoing elective high impact surgery in Radboudumc, Nijmegen. Patients will be grouped into 20 clusters based on diagnosis; colon cancer, rectal cancer, esophageal cancer, liver metastases from colorectal cancer, pancreato-biliary cancer, peritoneal carcinomatosis from colorectal cancer, abdominal aortic aneurysm (open and endovascular), renal cancer, bladder cancer, supratentorial meningioma, hip arthrosis, osteosarcoma, pulmonary cancer, thoracic aortic aneurysm, head and neck cancer, mouth cancer, breast reconstruction, ovarian cancer or endometriosis. The prehabilitation program intervention will commence in one cluster each month with the order of clusters determined by computer based randomization. The stepped-wedge design allow delivery of the intervention at an organizational level with evaluation of outcome measures at a patients level. Structuring the prehabilitation program intervention through a staged activation in a random order provides important methodological advantages. The design allows to control adoption bias and to adjust for time-based changes in the background level of patient care in statistical analysis. A key strength of stepped-wedge design is that the prehabilitation program can be offered to every patient who is undergoing elective high impact surgery in Radboudumc, Nijmegen.

This stepped-wedge cluster randomized trial will be combined with an observational cohort study performed in Radboudumc on surgery induced danger-associated molecule patterns (DAMPs) and innate immune changes in patients undergoing endovascular aneurysm repair(38). Patients within the care path 'abdominal aortic aneurysm' will undergo additional blood tests, according to protocol, to determine the effect of prehabilitation on the innate immune response (see also 8. METHODS).

| Cluster | Pre
(24 months) |     |     |   | Switching (20 months) |   |   |   |   |   |   |   |   |   |   |   |   |   |   |   |   |   |   |   |   |   | Post
(4 months) |   |   |  |
|---------|--------------------|-----|-----|---|-----------------------|---|---|---|---|---|---|---|---|---|---|---|---|---|---|---|---|---|---|---|---|---|--------------------|---|---|--|
| 1       | 0                  | ... | ... | 0 | 1                     | 1 | 1 | 1 | 1 | 1 | 1 | 1 | 1 | 1 | 1 | 1 | 1 | 1 | 1 | 1 | 1 | 1 | 1 | 1 | 1 | 1 | 1                  | 1 | 1 |  |

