## 8.2 Assignment to study

Patients eligible for surgery, according to inclusion- and exclusion criteria, will be assigned to either standard preoperative care or the multimodal intensive prehabilitation program, depending on the time frame and cluster in which the patient is included.

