- Degree of immunoparalysis; Monocyte HLA-DR (mHLA-DR) expression is chosen based on previous studies showing that 1) mHLA-DR expression is greatly reduced on postoperative day 2, and 2) mHLA-DR expression at this timepoint has predictive value for postoperative infections. mHLA-DR expression will be determined on the following time-points: baseline, prior to surgery, day 2 and week 6 postoperatively. Differences in mHLA-DR expression between 1) prehabilitation and standard of care, and 2) before and after prehabilitation, will be explored. mHLA-DR expression will be measured using Quantibrite methodology (BD Biosciences). This allows for quantification of the absolute number of HLA-DR monoclonal antibodies bound to each monocyte (mAb/cell), which corresponds to the number of HLA-DR molecules expressed on the cell surface. This standardized method is considered the gold standard for HLA-DR analysis and has shown excellent precision, robustness, and predictive value for the development of infections. Blood will be preserved using PROT1 reagent (Smart Tube Inc.), frozen, and analyzed batchwise on a single flow cytometer.
- To compare preoperative health behavior between patients in the control group and patients in the intervention group, a short questionnaire will be developed for each group including questions on physical activity (e.g. number of physiotherapy visits).

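### The exploratory mHLA-DR contrast between prehabilitation and standard care rests on one care path of at most two clusters, so its control numbers depend on the draw and its protection against time trends is weak

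*Protocol*

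**What the plan says.** Section 2 lists as a secondary objective: "Mechanistic level, i.e. innate immune response (degree of immunoparalysis"). Section 3 says who gives the blood: "Patients within the care path 'abdominal aortic aneurysm' will undergo additional blood tests, according to protocol". Table 5 (section 8.1.2) restricts the outcome to this path, "only in abdominal aortic aneurysm group", with samples at baseline, prior to anaesthesia, day 2 and week 6. Section 8.4 states the analysis aim: "Differences in mHLA-DR expression between 1) prehabilitation and standard of care, and 2) before and after prehabilitation, will be explored". It adds that samples are "frozen, and analyzed batchwise on a single flow cytometer".

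Condition is assigned by cluster and date. Section 8.2 has patients assigned "depending on the time frame and cluster in which the patient is included", and section 3 says: "The prehabilitation program intervention will commence in one cluster each month with the order of clusters determined by computer based randomization". The 24 pre-measurement months are retrospective. The prospective part is 20 switching months plus 4 post months.

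Two further places matter:

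- **Cluster count.** The list of diagnoses in section 3 has 19 items, with open and endovascular aneurysm as one item. Table 1 reaches 20 only by giving them separate rows.
- **Analysis.** Section 10.2 applies the generalized linear model of section 10.1 (cluster, treatment arm, linear time) to secondary outcomes. It also names t-tests and Mann-Whitney tests for continuous parameters at a single post-operative time point.

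**The concern.** A stepped-wedge design separates the intervention from calendar time by comparing many clusters that switch at different moments. mHLA-DR has one or two clusters, so little of that protection carries over. The retrospective pre-period, which supplies controls for complications, can hardly supply blood taken at four protocol time points. The remedy in section 10.4 for low recruitment does not help either: more retrospective records bring no blood, and more post months add only intervention patients.

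At stake is the mechanistic conclusion. A difference in mHLA-DR between conditions could reflect prehabilitation, a change in care over time or, in an unadjusted test, a different mix of open repair and EVAR. The number of controls available to examine this is left to the draw.

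**Working it through.** **The plan's own figure.** No sample size or power is given for mHLA-DR. The only power figure is 83% for the primary outcome. A log-binomial information calculation from Table 2 (24+20+4 months, risk ratio 0.80, two-sided 0.05 assumed) gives 78% with no trend, 81% with a 10% upward trend and 85% with a 20% trend. So 83% is reachable, and this point does not bear on it.

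**Inputs.** EVAR 120 a year = 10 a month; open repair 35 a year = 2.92 a month (Table 2). Accrual 60-80% (section 4.3). Prospective months: 20 + 4 = 24. From the section 3 diagram, a cluster at step k has k-1 control months and 25-k intervention months. Even monthly volumes and equally likely orders are assumed.

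**Control numbers if open and EVAR switch separately**

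- Mean control months per cluster: (0+1+...+19)/20 = 9.5.
- Expected control procedures: 9.5 x 10 + 9.5 x 2.92 = 95 + 27.7 = about 123, or 74-98 at 60-80% accrual.
- EVAR at step 1, so no controls: 1/20 = 5%. The same holds for open repair, so either one: 10%.
- EVAR in steps 1-3, so at most two months: 3/20 = 15%. Two months is 20 procedures, or 12-16 at 60-80% accrual.
- At least one of the two clusters in steps 1-3: 1 - (17 x 16)/(20 x 19) = 28.4%.
- Fewer than 20 controls in the whole path, over all 380 ordered pairs: 2.4%, or 6.6% at 60% accrual. The minimum is 2.9 procedures, never zero.

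**Time trends if they switch separately.** The mean gap between the switches is 7.0 months, and it is 2 months or less in 19% of orders. Within that gap, one condition is all open repair and the other all EVAR. Median standard errors over the 380 pairs (full volume, outcome SD = 1):

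| Adjustment | Standard error | Variance relative to first row |
|---|---|---|
| Cluster only | 0.128 | 1.0 |
| Cluster + linear time | 0.206 | (0.206/0.128)² = 2.6 |
| Cluster + month as category | 0.314 | (0.314/0.128)² = 6.0 |

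**Time trends if they switch together.** With c control and 24-c intervention months, the squared correlation of condition with linear time is 3c(24-c)/(24²-1), and the variance inflation is 1/(1-r²).

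- Step 2 (c = 1): r² = 3 x 1 x 23/575 = 0.120; inflation 1.14.
- Step 13 (c = 12): r² = 3 x 12 x 12/575 = 0.751; inflation 4.02.
- Step 1 (probability 1/20 to 1/19, about 5%): no controls.
- With month as a category the effect cannot be estimated at any step.

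**Unadjusted tests.** mHLA-DR at day 2 or week 6 is a continuous measure at a single post-operative time point, so the t-test or Mann-Whitney route in section 10.2 applies to it. Under separate switching, the open-repair share differs by more than 10 percentage points between conditions in 79% of orders. An unadjusted test carries that imbalance as well as any time trend.

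**The case against.** A reader might infer that this is an uncontrolled before-after comparison that may have no controls. The documents do not support that as a general statement. One cluster switches each month, so if open and EVAR are separate clusters, as the 20 rows of Table 1 imply, they cannot both be first. The path then always has some controls, and open repair and EVAR overlap in different conditions between their switches. That comparison is thin and crosses procedures, but it exists. The stronger reading fits only joint switching, which the 19-item list leaves open.

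Other parts of the defence also stand:

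- The model in sections 10.1 and 10.2 has cluster and time terms. Its cluster term deals with stable differences between procedures, so the 79% figure concerns only the unadjusted tests.
- The complication rates of 58% and 24% in Table 2 are not mHLA-DR levels. They indicate only that the two procedures carry different risk.
- Section 3 combines the trial with an observational cohort of EVAR patients. It could supply standard-care samples, although these would not be randomised, would cover EVAR only, and no use of them is described.
- Nothing says that the draw is unrestricted or that assay batches follow collection date. Freezing permits mixed batches, so batch confounding is only a possibility.
- The contrast is to be explored, and restricting sampling to one path is stated openly.

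The defence does not settle how the two procedures switch, does not remove the unadjusted tests, and does not change the dependence of control numbers on the draw.

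**Conclusion.** The concern holds in a limited form. The contrast rests on at most two clusters in which condition is fully determined by procedure and month. The expected control number is reasonable (about 123 procedures before accrual loss), but EVAR, 120 of the 155 aneurysm operations a year, has no controls in 5% of orders and at most two months' worth in 15%. Time adjustment costs a factor of 1.1 to 4.0 in variance under joint switching. Under separate switching, linear time costs a median factor of about 2.6, and the concurrent information is open repair against EVAR. The unadjusted tests in section 10.2 are the one part of the plan that is confounded as written.

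This assumes even monthly volumes, equally likely orders, k-1 control months at step k, no retrospective mHLA-DR samples and no use of the linked cohort. The primary endpoint is unaffected. The matter deserves correction, but it concerns one exploratory secondary outcome.

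**What to change.** 1. **Cluster structure.** State whether open repair and EVAR switch separately, and make the section 3 list agree with Table 1. Cost: wording.
2. **Analysis.** Analyse mHLA-DR only with a model adjusted for procedure, calendar time and the patient's own baseline value. Drop the t-test and Mann-Whitney test for this outcome. Keep day 2 as the key time point, since section 8.4 gives it as the reason for choosing the marker. Cost: wording, plus the wider but more honest standard errors shown above.
3. **Randomisation.** If the order is not yet drawn, keep both aneurysm clusters out of the earliest steps. Each excluded step guarantees one more control month: 10 EVAR procedures (6-8 at 60-80% accrual) and 2.9 open repairs (1.8-2.3). Open-repair controls stay few, so how many steps to exclude is a judgement. Cost: fewer permissible orders. If the order is already drawn, the other items still apply.
4. **Assay.** Preferably put samples from both conditions into each batch. Cost: some frozen samples wait longer.
5. **Reporting.** Present the result as exploratory evidence from one care path. Treat the within-patient change from baseline to before anaesthesia as supportive only: in prehabilitation patients alone it has no control, and it leaves out day 2. If the linked EVAR cohort is to supply controls, say so and call them non-randomised.
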